## Abstract

**Introduction:**

Weaning from ventilation is a complex process involving several stages that include recognition of patient readiness to begin the weaning process, steps to reduce ventilation while optimising sedation in order not to induce distress and removing the endotracheal tube. Delay at any stage can prolong the duration of mechanical ventilation. We developed a multicomponent intervention targeted at helping clinicians to safely expedite this process and minimise the harms associated with unnecessary mechanical ventilation.

**Methods and analysis:**

This is a 20-month cluster randomised stepped wedge clinical and cost-effectiveness trial with an internal pilot and a process evaluation. It is being conducted in 18 paediatric intensive care units in the UK to evaluate a protocol-based intervention for reducing the duration of invasive mechanical ventilation. Following an initial 8-week baseline data collection period in all sites, one site will be randomly chosen to transition to the intervention every 4 weeks and will start an 8-week training period after which it will continue the intervention for the remaining duration of the study. We aim to recruit approximately 10 000 patients. The primary analysis will compare data from before the training (control) with that from after the training (intervention) in each site. Full details of the analyses will be in the statistical analysis plan.

**Ethics and dissemination:**

This protocol was reviewed and approved by NRES Committee East Midlands—Nottingham 1 Research Ethics Committee (reference: 17/EM/0301). All sites started patient recruitment on 5 February 2018 before randomisation in April 2018. Results will be disseminated in 2020. The results will be presented at national and international conferences and published in peer-reviewed medical journals.

**Trial registration number:**

ISRCTN16998143.

Strengths and limitations of this studySedation AND Weaning In CHildren (SANDWICH) is the first large multicentre pragmatic randomised trial (approximately 10 000 children) evaluating a collaborative sedation and weaning protocol aimed at reducing the duration of invasive mechanical ventilation in critically ill children.From inception, SANDWICH has had strong involvement from medical and nursing staff, parents and patients, and a children’s research advisory group.The trial has an embedded cost-effectiveness and process evaluation.The primary outcome is patient relevant and was proposed by parents and children during feasibility work.A limitation may be the practicality of achieving all signed research and governance approvals to enable sites to start at the same time within the required start-up time frame.

## Introduction

On average more than 20 000 children are admitted to paediatric intensive care units (PICUs) in the UK and 65% of admissions to PICU require invasive mechanical ventilation (IMV) for acute respiratory failure.^1^ Weaning and extubation from IMV are key steps in the child’s recovery and indicate progression towards PICU discharge. Deferments in weaning impact on patient morbidity prolong PICU stay and bed availability.

Currently, there is no consensus on the optimal weaning approach from IMV in PICUs. Our feasibility study highlighted considerable variation in ventilator weaning practice: usually a slow reduction in ventilator support to a very low level prior to extubation and no test of early readiness for extubation on higher levels of support using a trial of spontaneous breathing.^2^ Furthermore, nurses’ roles are not optimally utilised to adjust ventilator settings due to lack of protocols to guide ventilator weaning and discontinuation.^3^ In many PICUs, very few nurses are engaged in weaning, most PICUs suspend changes to ventilator settings overnight and weaning only happens during the day.^2^

Weaning from ventilation involves: (1) recognition that the child is ready to begin the weaning process, (2) steps to reduce ventilation while optimising sedation in order not to induce distress and (3) removing the endotracheal tube. Delay at any stage can prolong the duration of IMV; therefore, an intervention targeted at helping clinicians to expedite this process safely should reduce the harms associated with IMV. However, the judgement and experience of clinicians are critical in guiding weaning from ventilation, as our feasibility study showed, there is wide variation in sedation and ventilator weaning practices, junior staff are rarely involved in the process and use of weaning protocols is rare.^2^

A Cochrane review of weaning protocols in mechanically ventilated children highlighted only three randomised trials.^4^ A two-centre trial (n=260), using an intervention incorporating daily screening and a spontaneous breathing trial (SBT), demonstrated a significant reduction of 32 hours (95% CI: 8 to 56 hours) in duration of IMV without additional harms.^5^ The smaller pilot studies using computer-driven protocols showed non-significant effects on duration of IMV, but significant reductions in weaning times (106 hours, 95% CI: 28 to 184; and 21 hours, 95% CI: 9 to 32).^6 7^ A recent paediatric multicentre cluster randomised trial in the USA (n=31 sites) evaluated a sedation weaning protocol that included an SBT and found no significant reduction in duration of IMV.^8^ However, the main focus of this intervention was the stringent sedative regimen (targeted sedation, arousal assessments, sedation adjustment every 8 hours and sedation weaning). In adults, a Cochrane review of protocolised weaning (17 trials) showed a 26% reduction in duration of IMV in favour of protocols and the most commonly used protocol was daily screening and SBT.^9^ Although results from adults cannot be applied directly to the paediatric population, the use of SBT as a weaning strategy shows promise and the paediatric systematic review indicates clinical uncertainty that is worthy of further evaluation.

Various intensive care unit studies have reported associations between rates of high interprofessional collaboration and lower patient mortality^10 11^ and improved clinician-to-clinician communication with reductions in length of stay.^12^ A team-led approach that improves engagement of all staff in early recognition of readiness and preparation for weaning ventilation has the potential to reduce duration of IMV and PICU length of stay and relieve pressures for beds. As 65% of nurses employed in UK PICU are Band 5 (junior) nurses, this would greatly increase the nursing contribution to the weaning process.^1^ Our feasibility study identified very few policies that specifically addressed sedation and weaning guidelines and staff interviews confirmed that a strategy for weaning sedation and ventilation was an important priority in most PICUs.^2^ Staff also disclosed continuing uncertainty about readiness to wean, the benefits of an extubation readiness test and its potential impact on duration of IMV in the UK.

The Sedation AND Weaning In CHildren (SANDWICH) trial has the capacity to generate new knowledge on the intervention, its cost-effectiveness and the implementation process. First, it will be large enough to provide reliable evidence for or against a combined ventilator/sedation weaning protocol allowing clear, strong recommendations to be made on the use of this potentially low-cost intervention. Second, it will determine the main organisational and process factors considered important for ensuring the intervention is optimally implemented in PICU.

## Methods

### Aim and objectives

The SANDWICH trial will evaluate the clinical and cost-effectiveness of a protocol-based intervention incorporating co-ordinated care in managing sedation and weaning ventilation in reducing the duration of IMV in children in PICU. Specific objectives are to determine if the intervention:

Reduces the duration of IMV in children irrespective of their expected ventilation duration (short or prolonged).Reduces length of PICU and hospital stayDoes not cause additional harm as assessed through review of adverse events and respiratory complications.Is cost-effective in the National Health Service.Is sustainable and acceptable to staff delivering care.

A process evaluation (PE) conducted alongside the trial will explore the processes involved in delivering the intervention, in order to identify factors and the mechanisms of their interaction that may impact on trial outcomes.

### Study design and setting

#### ​Setting

SANDWICH is a cluster randomised stepped wedge trial in 18 NHS PICUs. Participating PICUs provide clinical audit data to the Paediatric Intensive Care Audit Network (PICANet) database (www.picanet.org.uk). PICUs will be eligible if they agree to nominate local champions, comply with the protocolised weaning intervention and staff document a willingness to participate in training.

#### ​Design

The stepped wedge design involves sequential randomised rollout of the intervention over 4-week time periods (see figure 1). Randomisation will be conducted at the hospital site (cluster) level. In general, there is one PICU per site. In one site, there will be two PICUs participating. The site will be treated as one cluster for the purpose of randomisation, and the pair will be randomised to cross from control to intervention together to avoid intervention contamination within the site. In the analysis, we will treat these two PICUs as two separate clusters. This trial requires that all participating PICUs begin the control phase of the trial when the data collection period begins. There will be an initial 8-week period of baseline data collection during which the PICU will not be exposed to the intervention. Subsequently, every 4 weeks, one site will be randomly selected to transition to the intervention and start an 8-week training period during which the intervention will be rolled out. The PICU can neither be assumed to be exposed or not exposed during training so in these 8-week periods no patients will be recruited. Once a PICU crosses over to the intervention, it will remain exposed to the intervention for the remaining duration of the study. After the last PICU has crossed over and has fully transitioned to the intervention, there will be a final 8-week period during which all PICUs will be fully exposed.

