## Analysis

### Clinical evaluation

Baseline characteristics will be summarised by exposure and non-exposure to the intervention using summary statistics. PICUs will be classified as being exposed to the intervention on completion of the training period. The primary aim is to evaluate whether there is a difference in the duration of hours on ventilation before and after exposure to the intervention. We will use survival analysis (time to extubation) and estimate an HR for the intervention effect. This means that higher HRs will signify success of the intervention.

We will know exact survival times (ie, times until successful extubation) for most children, but children who die on ventilation, are transferred to another unit, are not weaned before transitioning to the training phase or are not weaned by 90 days will not have a known extubation time. We will treat such events as censored observations, making the assumption that children who are censored for any of these reasons will have an extubation time (ie, were or would have been removed from ventilation) greater than the time until they died or were transferred. These are plausible assumptions. In order to minimise any potential within cluster contamination, we will censor children when their PICU moves into the transition phase. When the PICU moves into the intervention phase, only new admissions will be included.

We will explore various models, but anticipate fitting a Cox proportional hazards model, perhaps with some treatment-by-covariate interaction to incorporate any non-proportionality. Allowance will be made for clustering using a frailty term for each PICU (this is similar to a random effect in a mixed-effects model). We will also adjust for calendar time, since the intervention is sequentially rolled-out. If a child is readmitted or transferred, they will be treated as new events and acknowledged within our analysis. Our primary estimate of the treatment effect will be a cluster and time-adjusted HR along with 95% CIs. Time adjustment is essential because this is a stepped wedge trial.

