## Sample size

The primary aim of this study is to determine whether the intervention can reduce the average number of hours on ventilation in eligible children. To inform the power calculation, we used PICU admissions data for the years 2014 to 2016 from units participating in the trial to determine parameters to inform the sample size calculation. The expected sample size is 9520 based on an average cluster size of 28 patients per 4-week block. In this trial, duration of ventilation is censored at the point of transitioning from the control to the training period, discharge to another hospital, at 90 days, death and receiving a tracheostomy, so applying censoring to this data set provided us with a homogeneous population that more accurately reflected the trial population. The mean duration of mechanical ventilation was 5.8 (SD 9.6) days and an Intracluster Correlation (ICC) of 0.005 (95% CI: 0.001 to 0.01). It is postulated that a reduction of 1 day on ventilation is both clinically important and achievable. While our primary analysis will be a survival analysis, no methodology currently exists to determine power in a stepped wedge trial for this outcome type. We therefore determined the power available assuming a continuous outcome. This is expected to be a conservative approach meaning that it should have slightly underestimated the power not having allowed for the time to event nature of the data.

The cluster sample size app (https://clusterrcts.shinyapps.io/rshinyapp) was used to update the sample size calculation given this information. Using this app and for the actual design of the trial (using the actual information on the number of clusters and number of steps) and using the following assumptions: no. clusters per sequence=1, ICC=0.005 (with consideration across the range 0.001 to 0.01), an exchangeable correlation structure, mean difference=1, SD=9.6, at 5% significance level, the power is approximately 80% for a cluster size of 28 (figure 2).

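### Minor: the two PICUs randomised together as one site are analysed as separate clusters with no site-level term, so any correlation between them is ignored

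*Protocol article*

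**What the plan says.** The Setting section gives the number of units: "SANDWICH is a cluster randomised stepped wedge trial in 18 NHS PICUs". The Design section makes the hospital site the unit of randomisation ("Randomisation will be conducted at the hospital site (cluster) level") and notes the exception: "In one site, there will be two PICUs participating". So 18 − 1 = 17 sites are randomised.

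For that one hospital, Design gives two rules:

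- Randomisation: "The site will be treated as one cluster for the purpose of randomisation". The article adds how this works in practice and its purpose: "the pair will be randomised to cross from control to intervention together to avoid intervention contamination within the site".
- Analysis: "In the analysis, we will treat these two PICUs as two separate clusters".

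The Clinical evaluation section carries the second rule into the primary model: "Allowance will be made for clustering using a frailty term for each PICU". It mentions no term for the site.

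The Sample size section assumes one cluster per sequence and states: "The expected sample size is 9520 based on an average cluster size of 28 patients per 4-week block". The article never states the number 17.

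**The concern.** A model with one frailty per PICU and nothing above it assumes that the 18 PICU effects are independent. For 16 single-PICU hospitals that is the usual assumption. For the pair it is doubtful: the protocol kept them together because it expected practice in one to reach the other, and units that close may also share staff habits, case mix and local policy. If their effects are correlated, the model counts the pair as two independent sources of information when they amount to fewer. The two-PICU hospital then gets somewhat too much weight and the standard error of the intervention effect comes out too small. In every scenario computed below the error runs in that direction or is nil.

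The protocol article fixes this choice explicitly and gives no reason for it. It is therefore not a detail merely left to the statistical analysis plan.

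**Working it through.** **Inputs from the article.** Design: 8-week baseline, one site crossing every 4 weeks, 8 weeks of training without recruitment, 8 final weeks with all sites exposed. Sample size: 28 patients per cluster per 4-week block, SD 9.6 days, difference 1 day, ICC 0.005 (range 0.001 to 0.01), exchangeable correlation, 5% significance (taken as two-sided).

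**Assumption, not in the article.** ρ is the correlation between the effects of the two PICUs at the shared hospital. It is varied from 0 to 1. Each of the two PICUs is taken to recruit 28 per block.

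**Step 1: reproduce the planned figures.** With 17 sequences there are 2 + 17 + 1 + 2 = 22 four-week periods: 2 baseline, 17 crossover steps, 1 more to finish the last site's training, and 2 final. Each cluster loses 2 periods to training, so it contributes 20.

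- N = 17 × 20 × 28 = 9,520, the stated figure exactly.
- 18 PICUs in the same 17 sequences would give 18 × 20 × 28 = 10,080.
- Power = Φ(δ/SE − 1.96). The SE comes from generalised least squares on cluster-period means, with fixed period effects and a random cluster effect. At ICC 0.005 the SE is 0.356 days and power is Φ(1/0.356 − 1.96) = 80.2%, matching the stated 80%. At ICC 0.001 and 0.01 it is 87.5% and 77.6%.

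The planning calculation therefore counts 17 clusters.

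**Step 2: the pair as two independent clusters.** Let Z hold the treatment and period indicators, V₀ the covariance with independent PICU effects, and V₁ the same covariance plus ρ × ICC × SD² between every cell of one PICU and every cell of the other. The model reports variance A = (Z′V₀⁻¹Z)⁻¹. The true variance is A Z′V₀⁻¹ V₁ V₀⁻¹Z A. With r = true SE / model SE, the true two-sided type I error is 2Φ(−1.96/r). The pair was placed in each of the 17 positions in turn, at ICC 0.005 and exchangeable correlation:

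| Sharing ρ | Mean excess of true SE | Largest excess (first or last position) | Middle position | Largest type I error |
|---|---|---|---|---|
| 0 | 0% | 0% | 0% | 5.0% |
| 0.5 | 0.3% | 0.75% | 0% | 5.17% |
| 1 | 0.6% | 1.5% | 0% | 5.35% |

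Example, ρ = 1 and the pair crossing first: model SE 0.3404, true SE 0.3455, ratio 1.015.

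**Step 3: wider assumptions, all with ρ = 1.**

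- ICC 0.001 to 0.01, with a fitted cluster autocorrelation of 0.8 to 1.0: the largest excess is 1.8%, with type I error 5.42%.
- True correlation decaying by a factor of 0.9 per period while the fitted model is exchangeable (ICC 0.005): sharing adds 1.3% on average and 2.6% at most. The model is already about 10% too optimistic there with unrelated PICUs, which is a separate matter.
- A site-specific intervention effect shared by the pair, with between-site SD 0.5 day or 1 day (ICC 0.005): sharing adds at most 2.5% or 4.4% to the SE, beyond what unrelated PICUs would show. The article gives no such SD.

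**Step 4: power.** At ICC 0.005, depending on the pair's position:

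- Two separate clusters, as the model would count them: 81.5% to 83.6%.
- Pair merged into one site cluster of 56 per block: 81.5% to 82.9%.
- Site-level effect with a fixed PICU indicator at that hospital: 81.5% to 82.8%, with an SE at most 1.1% above that of the separate-cluster model.

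All exceed the planned 80%.

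**The case against.** The case for leaving the plan alone is substantial, and most of it stands.

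- **Joint crossover answers contamination, not correlation.** Contamination means exposure leaking into a control unit, and crossing together deals with that. Correlated ventilation durations are a different matter, and the article gives no value for them. This stands as a limit: contamination risk makes correlation plausible but does not establish it, and the largest figures above assume complete sharing.
- **Two clusters in one sequence is ordinary.** A reader might infer that the analysis breaks the unit of randomisation. The documents do not support that. A stepped wedge model does not need each cluster to be randomised separately; it needs the correlation between clusters to be represented.
- **Planning is not affected.** A reader might infer that the sample size or power is inflated by counting 18 clusters. It is not: 9,520 is 17 × 20 × 28, and the eighteenth PICU adds data beyond the plan.
- **Degrees of freedom.** A reader might object that degrees of freedom based on 18 are too generous. The article states no small-sample correction, so that harm is hypothetical. It matters only as guidance for whatever correction is later chosen.
- **A nested random effect is barely estimable.** With a single pair, site and PICU variances can hardly be separated. This is why the fix uses a fixed indicator.

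What the objection does not remove is that the article fixes an independence assumption for the one pair of PICUs where it has given a reason to doubt it, and that following the randomised unit costs almost nothing.

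**Conclusion.** The point holds as a minor one. Seventeen sites are randomised and 18 clusters analysed, with no stated term for what the two PICUs at one hospital have in common. At the planning ICC with exchangeable correlation, the true SE exceeds the model's by between nothing (no sharing, or the pair in the middle of the rollout) and 1.5% (full sharing, first or last position), averaging 0.6% under full sharing. Type I error is at most about 5.35%. This alone is unlikely to change the trial's conclusion.

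These sizes rest on the article's own continuous-outcome approximation rather than the Cox frailty model, on equal recruitment of 28 per PICU per block, and on a degree of sharing that the article does not give.

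**What to change.** In Design and Clinical evaluation, replace the separate-cluster rule with three statements:

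1. The frailty is at the level of the randomised site (17 units), with a fixed PICU indicator at the two-PICU hospital so that a difference in level between its units is kept.
2. Any robust standard error or small-sample correction is based on 17 sites.
3. The trial has 17 randomised sites and 18 PICUs, and the 9,520 in Sample size is labelled as 17 clusters × 20 periods × 28 patients.

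The cost is one model term, a few words and a marginally wider confidence interval. No change to recruitment or to the power statement is needed.

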**Figure 1 F1:**
[figure not shown]
SANDWICH study flowchart. SANDWICH, Sedation AND Weaning In CHildren.

We have chosen the stepped wedge design over the conventional parallel cluster design for four main reasons. First, we have a limited number of clusters available (maximum 26 PICUs in the UK, but not all likely to agree to participate). With this limited number, the parallel design is infeasible as there are not sufficient clusters to allow detection of the important clinical effect. Second, feasibility work informed us that units are more likely to participate in the trial if they are guaranteed their unit will at some point receive the intervention.^2^ Third, it would be infeasible and more costly to deliver the intervention simultaneously to all units randomised to the intervention in a parallel design. Less important factors in our decision process, but none-the-less benefits of this design are the ability to estimate treatment effect heterogeneity (over time and clusters) and it allows for the possibility that the intervention may be tweaked as the trial progresses. This is important as while the intervention will be clearly documented in accordance with TIDieR guidelines,^13^ an intervention that is allowed to adapt to its setting has the best chance of success. Fourth, if the intervention is found to be effective, knowledge translation will be easier as PICUs participating can potentially continue post-trial maximising the benefits of any effects to the NHS and patients.

